##### Nutritional knowledge, attitudes and behaviours

Nutritional knowledge level is obtained by a quiz on dietary guidelines, physical activity, and health and nutrition relationship, for a score ranging from 0 to 100. Attitudes and behaviours are measured with the specifically designed Boire Manger Bouger (BMB; "Drinking, Eating, Moving") questionnaire. Satisfaction with food and physical activity and ability to follow guidelines for fruits and vegetables, dairy products, starchy food, drinks, sugary foods, number of meals and physical activity are explored. The environmental conditions of meals are also investigated.

Physical activity is measured by the International Physical Activity Questionnaire (IPAQ) [16]. The IPAQ assesses the frequency (days per week) and duration (minutes) of sitting and walking and of moderate and vigorous physical activity during the previous 7 days. Physical activity level is thus defined as low, moderate or high (the high level corresponds to nutritional guidelines).

##### Health

The EAT-40 [17], a validated and widely used questionnaire, screens for anorexic and bulimia symptoms. It is a self-reporting questionnaire with responses on a 6-point Likert scale ranging from 0, never, to 6, always. Four dimensions are explored: dieting, bulimia/food preoccupation, oral control and overall eating disorder [18]. Scores are estimated and the cut-off values used are those recommended by the authors.

The HAD [19,20] screens for depression and anxiety with 14 items on a 4-point Likert scale (range 0-3). The psychometric properties in the general population are acceptable [21]. The total score is the sum of the scores on the 14 items, and for each of the 2 subscales, the score is the sum of the scores on the respective 7 items.

The Duke Health profile [22,23], a 17-item generic self-reporting questionnaire explores perceived health and HRQoL with 10 dimensions; the physical, mental, and social dimensions are commonly used. High scores on the 0-100 scale indicate good HRQoL.

To facilitate interpretation, all scores are normalized to a 0-100 scale.

#### Process

Extensive process evaluation is considered a main part of the trial design. This evaluation aims to document how schools assigned to an interventional strategy implement it, and if control schools for this strategy implement interventions related to the theme of this strategy (e.g., environmental interventions implemented in a school that is a control for the environmental strategy). Other main aims are to collect information on the provision and receipt of the 3 nutritional interventions, determine the extent of possible contamination between schools, and report on the experience and impact of the PRALIMAP trial. Thus 2 domains -- implementation and participation -- are explored according to quality and quantity and from 4 points of view: students, PRALIMAP monitors, and school professionals as receivers of information from the PRALIMAP team and as providers of the intervention to students.

The process data sources are observation, stakeholders' interviews, and adolescent self-administered questionnaires.

##### Observation

Members of the research team observe the key processes in the implementation of interventional strategies in every high school and document the processes in activity reports. This observation includes regular meetings with high school professionals and teachers and an annual environmental survey. Meetings are organized once a month, are conducted by the PRALIMAP monitor, and aim to accompany and follow the performance of activities and to uphold the dynamics of the school's investment in the process. As described for the environmental strategy, the PRALIMAP monitor carries out an environmental survey of the headmaster, the financial administrator and the physical education teachers, whatever the strategy assigned to the school, at the beginning of every academic year.

##### Stakeholders' interview

A collective interview (focus group) is carried out with staff responsible for interventional strategies (high school professionals, head teachers) at the end of the 2 intervention years. It is lead by the process experts and psychologists of the PRALIMAP research team. Every PRALIMAP monitor is independently interviewed by use of a semi-structured interview guide by the PRALIMAP process evaluation lead at this time. The aim is to gather information about the content, delivery and stakeholders' appreciation of the intervention strategies over the 2 years (i.e., what was done, what stakeholders liked and disliked, the pros and cons of the interventions, their degree of satisfaction with the program, their appraisal of the benefit for students and recommendations for their own school and others). For the focus group, a full narrative description includes who was present, what was said, interactions between participants, the atmosphere, and the occurrence of significant events such as participants entering or leaving.

##### Student appreciation

A year-specific appreciation questionnaire is included at the T1 and T2 student report form. The survey aims to gain insight into students' perception and evaluation of the PRALIMAP trial (i.e., the school nutritional offerings, interactions with health and high school professionals, PRALIMAP activities participation, what they liked and disliked, how they perceived and incorporated interventional strategies and PRALIMAP as a whole).

### Data management and quality control

A Microsoft Access-based information system was developed to warehouse data (Microsoft Access 2003 v11.5614.6568, Seattle, WA, USA). At baseline, 15 keyboarders in 2006 and 18 in 2007 entered 18,105 and 28,836 data elements, respectively. The mean error rate was 30 per 10,000 data elements.

### Sample size

A total of 6,500 students were expected to attend grade 10 in the 24 high schools participating in the PRALIMAP trial. We anticipated approximately 5,590 participants on the basis of an approximately 86% mean participation rate of students in other nutritional studies [24-26]. Finally, from a sample size of 5,475, an average cluster size of 228 students and an anticipated intra-class correlation coefficient (ICC) of 0.005, we estimated a difference of approximately 4% in prevalence of overweight/obesity between the intervention and non-intervention arms at the end of PRALIMAP trial, assuming an alpha risk of 5% and a power of 80%. Power is assumed to be higher for other endpoints, namely, nutritional knowledge, attitudes and behaviours.

### Planned Analysis

The main judgment criteria consist of body size indicators: overall evolution of overweight and obesity prevalence, and among students with normal body size at trial entry, mean BMI evolution, proportion of students whose BMI evolution curve from baseline to the end of follow-up deviated from the IOTF and French norms for BMI between 16 and 18 years of age. Secondary judgment criteria refer to nutritional knowledge attitudes and behaviours and perceived health and quality of life, namely, the evolution in proportion of adolescents following nutritional guidelines and in mean nutritional knowledge score, the proportion of adolescents with eating disorders and high anxiety or depression scores, and finally Duke physical, mental and social dimensions scores.

Basic descriptive statistics were used to characterize the baseline participant population and interventions at both the participant and cluster levels. To produce accurate estimates of the used indicators in the Lorraine general population attending high schools, students' data were weighted by the product inverse of their high school probability to be included and their probability to participate. Intra-cluster similarity was analyzed by the ICC.

Students leaving high school, as well as students participating in the PRALIMAP over the intervention period will be described by a flow chart according to the CONSORT statement adapted to cluster randomised trials [27,28] and analyzed for possible selection bias.

Both cross-sectional and longitudinal analyses with cluster-specific methods are planned. General Estimating Equations (GEE) models will be used to take in account the hierarchical and longitudinal nature of the data. All analyses are planned at the individual student level on an intention-to-treat basis. Given the complexity of the analysis, details will be described more completely in the future.

The dose of intervention students receive will be estimated by the evaluation process in terms of a score developed by experts and will be taken into account on a per protocol analysis. Details of this analysis will be presented elsewhere.

SAS can accommodate the factorial clustered design and will be used for analysis (SASTM v9.2, SAS Inst., Cary, NC, USA).

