## Methods

### Design of the PRALIMAP trial

PRALIMAP is a stratified 2 × 2 × 2 factorial cluster randomised controlled trial. The units of randomisation are state high schools; 24 high schools participated in the trial in 2 waves: 8 in 2006 (wave 1) and 16 in 2007 (wave 2). The interventional strategies are organized by 2 academic years, and follow-up consists of 3 visits.

The PRALIMAP trial has been approved by the French consultative committee for treatment of information in health research (n°06.376) and the French data protection authority (n°906312). This trial is registered at ClinicalTrials.gov under NCT00814554 http://clinicaltrials.gov/ct2/show/NCT00814554.

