### Randomisation and student recruitment

The 24 high schools were assigned to receive the 3 strategies according to a 2 × 2 × 2 factorial cluster (high school) randomisation as described in Figure 1. Stratification was on department and type of education. In total, 8 groups, with 3 high schools in each group, were assigned to receive the following interventions:

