**Figure 3 F3:**
[figure not shown]
**Flow diagram of the initial phases of the progress of clusters and individuals in PRALIMAP**.

At cluster enrolment, the mean overall high school size was 812 students (range 283-1,893 students), and 29% had more than 1,000 students. The mean grade 10 size was 265.5 students (72-568). The mean grade 10 participants cluster size was 227.4 students (57-478). Thus, among the 6,371 grade 10 students, 5,458 (85.7%) underwent at least one baseline measurement, without any difference in participation in anthropometric and self-administered measurements. High school participation rates highly differed (from 72.0% to 99.1%) and were higher in general and technological than vocational high schools (86.6% vs 80.9%, p = < 0.0001) and in the rural administrative department of Vosges than in the other 3 departments (89.3% vs 85.1%, p = 0.0014). Finally, participation rates differed significantly but only slightly between strategy and control schools: educational strategy (86.9% vs 84.3%, p = 0.003), screening strategy (84.2% vs 87.1%, p = 0.001) and for environmental strategy (84.6% vs 86.7%, p = 0.013).

As compared with participants, non-participants were significantly older (p = < 0.0001) and more often had unemployed parents (p = 0.0143) and school backwardness (p < 0.0001). Boys and girls participated equally. Adolescents' baseline characteristics, overall and by strategy, are presented in Table 3, 4 and 5 and were similar to the French grade 10 population [29]. Students were in the expected age range, with more than 70% aged 15 years old. In total, 36%, 70%, 53% and 50.1% of students had school backwardness, were in grade 10 in a general and technological school, were girls and the family head was employed, respectively, as compared with 20%, 67%, 54% and 41%, respectively, in the French grade 10 population [29].

**Table 3 T3:** Baseline sociodemographic characteristics of students, overall and by assigned strategy

	**Overall^¶^**	**Educational** **strategy**		**Screening** **strategy**		**Environmental** **strategy**	
				
		**No**	**Yes**	**No**	**Yes**	**No**	**Yes**
	**N = 5,458**	**N = 2,483**	**N = 2,975**	**N = 2,771**	**N = 2,687**	**N = 2,794**	**N = 2,664**
	**%**	**%**	**%**	**%**	**%**	**%**	**%**
							
**Mean age (years)**	15.8*	15.7^¥^	15.7^¥^	15.7^¥^	15.7^¥^	15.7^¥^	15.7^¥^
**Gender (% girls)**	52.9	56.8	53.6	56.5	53.6	54.8	55.4
**General and technological course**	69.7	78.6	83.3	77.9	84.5	78.9	83.5

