The PRALIMAP is a pragmatic trial where interventions were implemented in the real context of high schools. Effectiveness [56] is evaluated through body composition measurements, nutritional behaviour and knowledge outcomes, as was recommended by some authors [35,45,57]. The PRALIMAP outcomes rely on anthropometric data collected by high school nurses and on self-reported measures such as knowledge and behaviours collected in the classroom setting. At baseline, we achieved a high participation rate for both types of measurements (85.7%). The availability of the Board of Education database allows for comparison of the sociodemographic differences between participants and non-participants and suggests a probable higher non-participation rate among overweight students. However, non-participation in the PRALIMAP measurements is similar across arms. The turnover with entry level and attrition at each grade is common in schools and is likely to reduce power and even introduce bias if these data differ by randomisation arm. The design offers the opportunity to analyse the data in a longitudinal cohort approach, as well as in a repeated cross sectional approach. It offers the opportunity to combine hard outcomes (body size) with declared and perceived outcomes [58] (self-administered questionnaires) to explore the hypothetical cause from knowledge to health. Questionnaires used were standardised internationally or specifically designed for PRALIMAP. The time interval between the second and last visit measurements was shorter in the vocational than general and technological high schools, but the stratification design allowed us to control for this difference.

A remarkable feature of the PRALIMAP is the extensive and comprehensive process evaluation. The trial was designed to investigate not only the outcomes relating to nutritional behaviours but also the processes involved in developing and implementing the intervention strategies, as well as the type of nutritional activities provided in the control schools for each strategy. This feature can help interpret observed relationships between the interventions and outcomes. A specific work is planned to provide an estimation of the dose of intervention, which will allow for more intensive analysis beyond a simple interpretation task by performing a per protocol statistical analysis including the dose of each strategy implemented in each high school.

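### The printed baseline participation p-values by strategy treat students as independent although schools were randomised; with the school as unit the stated significance is not supported, and the Discussion says something different

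*Protocol article*

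**What the plan says.** **Unit of randomisation.** The design section reports "24 high schools participated in the trial in 2 waves: 8 in 2006 (wave 1) and 16 in 2007 (wave 2". Randomisation and student recruitment describes "8 groups, with 3 high schools in each group", so each strategy's main effect compares 12 schools with 12. It adds: "Stratification was on department and type of education".

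**Participation results.** Inclusion data reports that 5,458 of 6,371 grade 10 students took part (85.7%) and that school rates ran from 72.0% to 99.1%. It then says "participation rates differed significantly but only slightly between strategy and control schools":

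- educational: 86.9% v 84.3%, p = 0.003
- screening: 84.2% v 87.1%, p = 0.001
- environmental: 84.6% v 86.7%, p = 0.013

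The Discussion, looking back at the same baseline, says "non-participation in the PRALIMAP measurements is similar across arms".

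**Planned outcome analysis.** Planned Analysis says "General Estimating Equations (GEE) models will be used to take in account the hierarchical and longitudinal nature of the data", at student level and by intention to treat. It names no variance estimator, test or reference distribution, and closes with "Given the complexity of the analysis, details will be described more completely in the future".

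**The concern.** A comparison between randomised arms carries only as much information as there are randomised units. Here that is 24 schools, and participation varied widely between them. A test that counts some 6,400 students as independent leaves out the school-to-school variation and makes small differences look firmer than they are.

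Two things are at stake. First, a reader who wants to know whether recruitment differed by arm is told that it did, at p-values down to 0.001, and later that it did not. Second, the planned GEE analysis rests on the same 24 schools. If the robust variance were used there without a small-sample adjustment, strategy effects would be declared more often than the nominal 5% under the null.

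**Working it through.** **1. Reproduce the printed p-values.** Inputs are the participants per arm (Table 3) and the printed rates (Inclusion data). Eligible students = participants / rate. The test is z = difference / √[p̄(1−p̄)(1/N₁+1/N₀)], with p̄ ≈ 0.857.

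| Strategy | Eligible, yes / no | Difference | SE | z | p | Printed |
|---|---|---|---|---|---|---|
| Educational | 2,975/0.869 = 3,423; 2,483/0.843 = 2,945 | 2.6 points | 0.88 | 2.96 | 0.0031 | 0.003 |
| Screening | 2,687/0.842 = 3,191; 2,771/0.871 = 3,181 | 2.9 | 0.88 | 3.30 | 0.0010 | 0.001 |
| Environmental | 2,664/0.846 = 3,149; 2,794/0.867 = 3,223 | 2.1 | 0.88 | 2.39 | 0.017 | 0.013 |

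The rebuilt denominators sum to within a few students of the stated 6,371. When the total is fixed at 6,371 and every denominator consistent with the rounded rates is tried, p ranges over 0.0028-0.0034, 0.0008-0.0010 and 0.0134-0.0187. The first two printed values match; the third lies at the edge of its range. All three are consistent with a test that ignores the school.

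**2. School as the unit.** SE = SD × √(1/12 + 1/12) = 0.408 × SD, with t on 24 − 2 = 22 df. The article gives no between-school SD, so two values are assumed from the range of 99.1 − 72.0 = 27.1 points:

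- SD about 7: 27.1/3.9, where 3.9 SDs is roughly the expected range of 24 normal values.
- SD about 4: close to the smallest possible, with one school at each extreme and 22 at the midpoint, √(2 × 13.55²/23) = 4.0.

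| Strategy | SD 4 (SE 1.63): t, p | SD 7 (SE 2.86): t, p |
|---|---|---|
| Educational | 1.59, 0.13 | 0.91, 0.37 |
| Screening | 1.78, 0.09 | 1.01, 0.32 |
| Environmental | 1.29, 0.21 | 0.73, 0.47 |

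**3. Cross-check by design effect.** DE = 1 + (265.5 − 1) × ICC, where 265.5 is the mean grade 10 size; z is divided by √DE and referred to t on 22 df.

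| ICC | DE | Educational | Screening | Environmental |
|---|---|---|---|---|
| 0.005 | 2.32 | 0.065 | 0.041 | 0.13 |
| 0.01 | 3.65 | 0.14 | 0.10 | 0.22 |
| 0.02 | 6.29 | 0.25 | 0.20 | 0.35 |

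Only screening stays below 0.05, and only at an ICC of about 0.005. That is the value anticipated for overweight/obesity in Sample size ("from a sample size of 5,475, an average cluster size of 228 students and an anticipated intra-class correlation coefficient (ICC) of 0.005"), not one given for participation. For participation, ICC ≈ (SD² − 0.857 × 0.143/265.5)/(0.857 × 0.143), which is about 0.009 at SD 4 and 0.036 at SD 7.

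**4. What an uncorrected GEE test would do.** Null trials were simulated with 24 schools, 3 per cell, 57-478 students per school, prevalence 14.9% + 4.6% = 19.5%, beta-binomial clustering with ICC 0.005 or 0.02, and a logistic GEE clustered on school at a single visit. Rejection rates for a strategy main-effect term at nominal 5%:

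| Model | Uncorrected robust Wald z |
|---|---|
| Three main effects (4 parameters) | 8.5-8.8% |
| 8 parameters (all interactions, or main effects with department and type) | 13.5-14.6% |
| 12-13 parameters | 21-23% |

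With a Kauermann-Carroll variance and t on 24 minus the number of parameters, these rates are about 5-6.5%. A contrast of one cell with control (3 v 3 schools) rejects in 19% uncorrected and still in about 11% with Kauermann-Carroll and t on 16 df, because only six schools inform it.

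**The case against.** **The two statements need not clash.** Inclusion data says the differences were slight, and gaps of 2.1 to 2.9 points can fairly be called similar in size. This stands in part: the Discussion wording is defensible as a judgement of magnitude. It does not rescue the statement of significance, which is about chance and uses the wrong unit.

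**These are descriptive baseline tests, and the error overstates imbalance rather than hiding it.** Correct, and it limits the consequence. Recomputing would bring the results closer to the Discussion. Nor does the planned selection-bias analysis rest on these three p-values: it concerns leavers and participants over the intervention period, and the Board of Education database allows a separate comparison of participants with non-participants.

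**The school-level p-values rest on a guessed SD.** Also correct, which is why a range is shown. Part of the spread comes from school type and department, so a stratified test could give somewhat smaller p-values.

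**A reader might infer that the planned GEE has no small-sample correction, and hence that every strategy test will run at two to three times its nominal level.** The article does not support that. It neither specifies nor excludes a correction and defers the details, which is normal for a condensed article. The inflation depends on the test and the model: a GEE score test with main effects only gave 6.4%. Three schools per cell is the relevant number for single-cell contrasts; main effects use 12 v 12.

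**Conclusion.** The point holds for the printed participation tests. They match tests that treat students as independent, and the significance they claim is not supported once the school is the unit: p is about 0.09-0.21 at a between-school SD of 4 points and 0.32-0.47 at 7 points. The one exception, screening at 0.041, needs an ICC of about 0.005, below the roughly 0.009 implied by even the smallest SD that the printed range allows. The statement also fits poorly with the Discussion.

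These figures assume two-sided tests, denominators rebuilt from rounded rates, pooled rate differences standing in for differences of school means, and SDs inferred from a range.

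The GEE part is a conditional risk and not an error shown in the plan. If an uncorrected robust Wald z-test is used, type I error is about 9% for main effects, 13-15% with 8 parameters and above 20% with 12-13. The simulation assumes beta-binomial clustering, an assumed distribution of school sizes within the printed range, and unrestricted rather than stratified allocation.

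**What to change.** 1. Under Inclusion data, recompute the three strategy comparisons with the school as unit (a school-level t or permutation test, preferably respecting the strata), or remove the p-values and give the rates with the spread across schools.
2. Reword that paragraph and the Discussion sentence so that they say the same thing, for example differences of 2 to 3 points with no clear evidence of a difference between arms beyond school-to-school variation, if the recomputation bears this out.
3. In the analysis plan, state that the school is the independent cluster in every GEE, with students and visits nested in it. Specify a small-sample corrected robust variance (such as Kauermann-Carroll) with a t reference on 24 minus the number of school-level parameters. Add a school-level or permutation check, above all for single-cell contrasts, where that correction alone is not enough.

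The school participation counts are already held, so items 1 and 2 cost a short re-analysis and a few words. Item 3 costs a few lines of text and code and somewhat wider confidence intervals.
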